#### Quantitative analysis: phase IIb

2.4.3

All quantitative analyses will be conducted using Stata (version 19; StataCorp LLC, College Station, TX, USA). Normality of continuous variables will be assessed using the Kolmogorov–Smirnov and Shapiro–Wilk tests, with non-parametric methods applied as appropriate. Continuous variables will be summarized using means and standard deviations, and categorical variables using frequencies and percentages. Between-group comparisons will be conducted using Student's *t*-tests for continuous variables and chi-square tests for categorical variables. To examine changes in outcomes over time, repeated-measures analysis of variance (ANOVA) will be used to assess group-by-time interactions across baseline, 6-month, and 12-month assessments, with Bonferroni-adjusted *post hoc* comparisons. Models will adjust for baseline values of outcome measures. Statistical significance will be set at *P* < 0.05. Sensitivity analyses will be conducted using multiple imputation to address missing data and assess the robustness of findings.

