**Methods**	Strategies consonant with patients' culture	Use of visual aids and simple definitions to describe the content clearly.
**Context**	Consideration of contextual factors	Integration of menu plan based on the 4A framework and what-up messages for reminding, encouraging, motivating, and self-efficacy.

The intervention integrates individual nutrition counseling with group education to target multiple mechanisms of behavior change. Group sessions were designed to enhance family involvement, strengthen coping skills, and increase self-efficacy through guided practice, goal setting, and progress monitoring, while individual sessions supported personalized dietary planning and goal refinement. Consistent with MNT practice guidelines and prior behavioral interventions (38, 39), the program was structured to include 12 sessions, (four individual and eight group), considered sufficient to support knowledge acquisition, skill development, and the adoption of sustainable dietary behaviors (40–42).

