#### Phase IIa sample

2.3.1

A single-arm feasibility design will be used to enroll 30 adults with T2D. Eligible participants will (1) self-identify as Beninese; (2) be aged 40–65 years; (3) have a clinical diagnosis of T2D for at least one year; (4) have an HbA1c level >7% at enrollment; (5) have a family member willing to participate or provide ongoing support; and (6) be willing to commit to the study protocol and attend scheduled sessions. Participants will be recruited from the pool of 512 individuals who participated in Phase Ib. The sample size of 30 was selected in accordance with recommendations for pre-pilot and feasibility studies (43). The intervention will include two individual sessions (45–60 min each) and eight group sessions (90–120 min each). Sessions will be delivered by six trained dietitians or nutritionists, with each group of 10 participants assigned two facilitators experienced in health promotion, trained in MNT, and committed to maintaining protocol fidelity.

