#### Phase IIb sample

2.4.1

A total of 60 adults with T2D will be enrolled and randomized in a 1:1 ratio to either the intervention group (OSanDiaBé) or a wait-list control group receiving usual care. Randomization will be conducted after screening and informed consent using a computer-generated randomization sequence. To minimize potential bias, the principal investigator will be aware of group allocation, while physicians, data collectors, and laboratory personnel will remain blinded. Participants will be informed of their group assignment following randomization. The target sample size (*n* = 60; 30 per group) is consistent with recommendations for pilot randomized trials and is intended to support intervention refinement and effect size estimation for subsequent efficacy studies (58). Findings from Phase IIa will further inform final sample size considerations for later trials.

Participants will be recruited from six collaborating health centers using provider referrals, peer referrals, flyers, and word-of-mouth outreach. Eligibility criteria include: self-identification as Beninese; age 40–65 years; a clinical diagnosis of T2D for ≥1 year; uncontrolled diabetes (HbA1c >7%); availability of a supportive family member; and ability to provide written informed consent. Participants must be deemed suitable for group-based education and general dietary and lifestyle guidance by the referring healthcare provider. Exclusion criteria include pregnancy, recent major cardiovascular events (e.g., stroke or congestive heart failure), clinical conditions requiring specialized dietary management, or current participation in a similar nutrition program, to minimize contamination and ensure participant safety.

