#### Phase IIb procedures

2.4.2

The primary objective of Phase IIb is to evaluate the preliminary efficacy of OSanDiaBé in improving dietary adherence (primary behavioral outcome), and glycemic control (HbA1c) (primary biomedical outcome), as well as related T2D risk factors. Prior to study initiation, intervention materials will be finalized based on feedback from Phase IIa while preserving the core dietitian-led MNT framework. Facilitators will receive standardized training and lesson plans to ensure implementation fidelity.

As outlined in Table 2, participants in the intervention group will attend four individual sessions (45–60 min each) and eight group sessions (90–120 min each) during the first 6 months. The first two individual sessions will be delivered before and after the group sessions within the initial 3 months, followed by 2 monthly booster sessions between months 3 and 6. Group sessions will be delivered weekly or biweekly over an eight-week period. Intervention participants will receive the OSanDiaBé resource package, including a participant workbook, and an individualized Eating Plan based on the 4A food security framework. No intervention contact will occur between months 6 and 12. Participants in the wait-list control group will complete assessment visits at baseline, 3 months, 6 months, and 12 months and will receive usual care during the study period. Following completion of the 12-month assessment, they will be offered the OSanDiaBé intervention delivered by the same trained facilitators to ensure equitable access.

**Table 2 T2:** Overview and timeline of the OSanDiaBé intervention and assessments (ORBIT Phase IIb).

**Study activities**	**Baseline (Month 0)**	**3 months (End of Core Delivery)**	**6 months (End of Active intervention)**	**12 months (Maintenance Follow-up)**
Enrollment, informed consent, and randomization	X			
Usual care (control group; standard clinical management throughout study)	X	X	X	X
Individual MNT sessions (*n* = 4; intervention group)	X	X	X	
Group MNT sessions (OSanDiaBé; *n* = 8; intervention group)		X (Months 0–3)		
Dietary assessments (e.g., dietary adherence, diet quality/intake screener)	X	X	X	X
Psychosocial assessments (family functioning, self-efficacy, diabetes knowledge, quality of life)	X	X	X	X
Anthropometric measurements (weight, height, BMI, waist circumference)	X	X	X	X
Metabolic assessments (HbA1c, blood pressure, lipid profile)	X	X	X	X

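### Phase IIb teaches only the intervention arm in groups, but its planned tests assume independent participants; if outcomes correlate within session groups, standard errors are too small

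*Protocol article*

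**What the plan says.** **Allocation (section 2.4.1).** Individuals are randomized: "A total of 60 adults with T2D will be enrolled and randomized in a 1:1 ratio". The sample size rests on pilot-trial guidance, not on a power calculation: "The target sample size (*n* = 60; 30 per group) is consistent with recommendations for pilot randomized trials".

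**Delivery (section 2.4.2 and Table 2).** The intervention arm has four individual and eight group sessions. On timing: "Group sessions will be delivered weekly or biweekly over an eight-week period". Controls receive usual care and are offered the programme only after the 12-month visit. No group size, number of groups or number of facilitators is given for Phase IIb. For Phase IIa, section 2.3.1 is specific: "with each group of 10 participants assigned two facilitators experienced in health promotion".

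**Role of the group (section 2.2.1).** Group work is an intended route to the effect: "Group sessions were designed to enhance family involvement, strengthen coping skills, and increase self-efficacy through guided practice, goal setting, and progress monitoring".

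**Analysis (section 2.4.3).** "Between-group comparisons will be conducted using Student's" t-tests for continuous variables, with chi-square tests for categorical ones. For change over time, "repeated-measures analysis of variance (ANOVA) will be used to assess group-by-time interactions across baseline, 6-month, and 12-month assessments". Models adjust for the baseline value of the outcome. "Statistical significance will be set at *P* < 0.05". The only sensitivity analysis named is multiple imputation for missing data. Session group, facilitator and ICC do not appear in the analysis.

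**The concern.** People taught together share facilitators, peers and the course of the discussion, so their outcomes may resemble each other more than those of people taught apart. Dietary adherence, the primary behavioral outcome, also includes facilitator-based monitoring; where facilitators rate their own group, that is a second source of shared variation. Controls have neither. The clustering therefore sits in one arm only, and all three named methods ignore it.

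With positive correlation, the mean of the intervention arm is less precise than 30 independent people would make it, and the test does not see this. Phase IIb is meant to give initial effect estimates and to judge readiness for a full efficacy trial, and it states between-arm hypotheses with a significance threshold. Overstated precision bears on both uses. Since the article itself names the tests, this is a mismatch within the stated plan and not a detail left to a document not shown.

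**Working it through.** **No figure to reproduce.** The article gives no effect size, SD, power or ICC for Phase IIb. The check therefore concerns only the behaviour of the stated test.

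**Inputs from the article**
- 30 per arm, individual 1:1 randomization (2.4.1).
- Threshold 0.05 (2.4.3). Sidedness is not stated there; two-sided is assumed.
- Group sessions in the intervention arm only (2.4.2).

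**Assumptions**
- Group size m = 10, stated for Phase IIa only (2.3.1). Then 30/10 = 3 groups. In Phase IIa, 3 groups × 2 facilitators gives the six facilitators stated there, so group and facilitator pair coincide. Sizes 6 and 15 are shown as a range.
- ICC from 0 to 0.10, because none is given.

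**Formulas**
- Design effect in the intervention arm: DE = 1 + (m − 1) × ICC. Control arm: 1.
- True SE / reported SE = √((DE + 1)/2).
- Approximate type I error = 2 × (1 − Φ(1.96 / ratio)).

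Example, m = 10 and ICC = 0.05: DE = 1 + 9 × 0.05 = 1.45; ratio = √(2.45/2) = 1.107; 1.96/1.107 = 1.771; type I error about 0.077. The 30 intervention participants carry the information of 30/1.45 = 20.7.

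**Results, 3 groups of 10 versus 30 unclustered controls, t-test at one time point**

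| ICC | DE | SE ratio | Type I, formula | Type I, simulated (200,000 runs) |
|---|---|---|---|---|
| 0 | 1.00 | 1.000 | 0.050 | 0.050 |
| 0.01 | 1.09 | 1.022 | 0.055 | 0.055 |
| 0.02 | 1.18 | 1.044 | 0.060 | 0.060 |
| 0.05 | 1.45 | 1.107 | 0.077 | 0.077 |
| 0.10 | 1.90 | 1.204 | 0.104 | 0.105 |

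Simulation error moves the third decimal: repeat runs gave 7.6% to 7.7% at ICC 0.05. At ICC 0.05, groups of 6 give 6.4% and groups of 15 give 9.3%.

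**Possible remedies, same setting**
1. *Group-mean analysis with Satterthwaite degrees of freedom* (60,000 runs). Type I error is 5.8% at ICC 0, 5.6% at 0.02, 6.1% at 0.05 and 6.3% at 0.10. At ICC 0.05 the mean interval width rises from 1.025 to 1.401 SD (1.401/1.025 = 1.37), and rejection at a true difference of 0.74 SD falls from 78% to 58%.
2. *Estimating the group variance.* With 3 groups of 10 at ICC 0.05, the ANOVA estimate is zero or negative when F(2, 27) falls below 0.95/1.45 = 0.655. That has probability 1 − (1 + 2 × 0.655/27)^(−13.5) = 0.47. A random-effect model would often collapse to the unclustered analysis.
3. *Intervention-arm variance multiplied by DE at a fixed ICC* (100,000 runs). When the assumed ICC equals the true one, type I error is 5.1%, 5.1% and 5.2% at 0.02, 0.05 and 0.10. If 0.05 is assumed and the truth is 0.10, it is 7.3%; if the truth is 0, it is 3.0%.

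**The case against.** **Every size rests on assumptions.** This stands. No ICC is given, and the group size is borrowed from Phase IIa. At ICC 0.01 to 0.02 the type I error is 5.5% to 6.0%, which matters little in a 60-person pilot. Only the direction, for any positive ICC, is free of these assumptions.

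**Clustering may be weak where it counts.** This is plausible. Group sessions end within the first 3 months, later contact is individual and then absent, and the hypotheses concern 6 and 12 months. Each person has an individualized plan, home-based counseling is available to those who cannot attend, and HbA1c is measured by blinded laboratory staff. The ICC for HbA1c may be at the low end; the article settles it neither way. The argument is weaker for dietary adherence, part of which is facilitator-rated.

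**The figures describe one t-test, not the longitudinal model.** This also stands. The ANOVA and the baseline-adjusted models were not simulated. They make the same independence assumption, and the relevant ICC would be that of the change or baseline-adjusted outcome, but the percentages should not be read across to them.

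**A random-effect model should be the primary analysis.** A reader might infer this. With about three groups it is not clearly better: in the group-mean version the error rate stays near 6%, and the interval widens by 37% where the true SE is only 11% larger.

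**Phase III will be too small.** A reader might infer this as well. The article shows no Phase III calculation, so nothing indicates that clustering will be ignored there.

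**Conclusion.** The point holds in conditional form. Phase IIb is partially nested, the stated methods assume independence, and nothing elsewhere in the article corrects for it. If outcomes within session groups are positively correlated, the standard errors and P values for both primary outcomes are too optimistic. With three groups of 10, a single-time-point t-test at nominal 5% runs at about 6%, 7.6% and 10.5% for ICC 0.02, 0.05 and 0.10, with a true SE 4%, 11% and 20% larger than reported. Both the ICC and the Phase IIb group size are assumed.

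The article does not support a flat statement that the standard errors are too small, because the ICC is unknown and could be near zero. The effect estimate is not biased by this, and N = 60 is not shown to be wrong. The change is worth making before Phase IIb starts, since group membership not recorded during delivery may be hard to recover.

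**What to change.** In section 2.4.3, with the matching description in 2.4.2:

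1. State the planned number and size of Phase IIb session groups and the facilitators per group, and record the session group and facilitator of each intervention participant.
2. Report the between-arm estimates for both primary outcomes with intervals in which the intervention-arm variance is multiplied by 1 + (m − 1) × ICC, over a prespecified ICC range, for example 0.01 to 0.10.
3. Add a partially nested mixed model as a sensitivity analysis: random session-group effect in the intervention arm only, baseline value as covariate, and small-sample degrees of freedom (Satterthwaite or Kenward-Roger). Do not make it the mandatory primary model.
4. Report the between-group variance descriptively, with its imprecision, for Phase III planning.

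The cost is some analysis wording and the group and facilitator identifiers. No visit, procedure or sample size changes. The downside is wider intervals, about 11% at ICC 0.05 with groups of 10, and a group variance that about three groups will estimate poorly. The fixed-ICC intervals are right only if the range covers the true value, so the whole range should be shown and not one chosen figure.

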### Phase IIb: pilot study

2.4

Phase IIb will be conducted following completion of Phase IIa to evaluate the preliminary efficacy of the OSanDiaBé intervention compared with usual care among adults with T2D. Consistent with the ORBIT framework, this phase is designed to generate initial estimates of intervention effects on key behavioral and biomedical outcomes and to assess readiness for a subsequent, fully powered efficacy trial. Usual care consists of standard clinical management, including routine blood glucose monitoring, medication adherence counseling, and general lifestyle advice delivered in routine practice (57). We hypothesize that participants receiving OSanDiaBé will demonstrate greater improvements in dietary adherence and greater reductions in HbA1c at 6 months compared with those receiving usual care. We further hypothesize that these improvements will be maintained at 12 months following the end of active intervention contact.

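### Phase IIb uses baseline both as a repeated response and as a covariate, so the group-by-time test is not the baseline-adjusted analysis that the plan states, and no 6-month contrast is named.

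*Protocol article*

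**What the plan says.** The section on quantitative analysis for Phase IIb describes one model for the outcomes: "repeated-measures analysis of variance (ANOVA) will be used to assess group-by-time interactions across baseline, 6-month, and 12-month assessments", "with Bonferroni-adjusted *post hoc* comparisons". Its next sentence is "Models will adjust for baseline values of outcome measures". It does not say how the baseline value enters, and it mentions no baseline-by-time term. The significance rule is "Statistical significance will be set at *P* < 0.05".

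The introduction to the pilot study puts the main hypothesis at one time point: "greater improvements in dietary adherence and greater reductions in HbA1c at 6 months compared with those receiving usual care". A second hypothesis concerns maintenance: "We further hypothesize that these improvements will be maintained at 12 months following the end of active intervention contact".

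The sample section sets 60 patients, 30 per arm, by pilot-trial convention. It gives estimating an effect size for later trials as one purpose of that number. Entry requires HbA1c above 7%.

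**The concern.** The two sentences on the model do not work together. Once baseline is one of the three repeated responses, the group-by-time term compares the arms on change from baseline. Adding the same baseline value as a patient-level covariate affects only differences between patients, and the interaction does not use those. On the baseline rows the outcome is regressed on itself.

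A reader of the results would take the interaction to be adjusted for baseline in the ANCOVA sense, and as written it would not be. The group main effect does respond to the covariate, but it averages over the pre-treatment visit and is not a usable treatment effect.

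The hypothesis also concerns 6 months, whereas the named test is a 2-df interaction over three visits. An overall F test gives no effect estimate, and the contrast that would give one is not specified. For a pilot whose main product is an effect estimate to carry forward, both the precision and the definition of that estimate matter.

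**Working it through.** **No figure to reproduce.** The 60 patients have no effect size, SD, correlation or power behind them, so the check is of the model itself.

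**Step 1: what the covariate can do.** Write the stated model for patient i at visit t (0, 6, 12 months), with arm A, baseline value B and patient effect u:

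Y(i,t) = μ(t) + γ·A(i) + δ(t)·A(i) + β·B(i) + u(i) + e(i,t)

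Subtract the baseline row from the 6-month row:

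Y(i,6) − Y(i,0) = [μ(6) − μ(0)] + [δ(6) − δ(0)]·A(i) + e(i,6) − e(i,0)

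The terms β·B(i) and u(i) have gone. With complete data the interaction is estimated from such within-patient differences, so β has no effect on it.

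**Step 2: numerical confirmation.** One simulated data set, 30 per arm, assumed correlation 0.5, visits at 0, 6 and 12 months:

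| Model | Group-by-time test |
|---|---|
| No baseline covariate | F(2,116) = 4.2749, p = 0.0162 |
| Baseline as main effect | F(2,116) = 4.2749, p = 0.0162 |
| Baseline-by-time added | F(2,114) = 4.764, p = 0.0103 |

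A random-intercept mixed model agreed. The interaction estimates (−0.5038 at 6 months, −0.6344 at 12 months) and their standard error (0.2291) were the same with and without the covariate. Only the between-patient variance moved, from 0.401 to 0.041.

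**Step 3: validity.** In 4,000 simulated trials with no effect, at each of four assumed correlations (0.3, 0.5, 0.7, 0.8), the group-by-time test rejected in 4.7% to 5.4%.

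**Step 4: precision, equal SDs.** Let ρ be the correlation of baseline with month 6, and σ the common SD. Per patient, the variance of the change is 2(1 − ρ)σ², and the ANCOVA residual variance is (1 − ρ²)σ². The ratio is

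2(1 − ρ)/(1 − ρ²) = 2/(1 + ρ)

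| Assumed ρ | Variance ratio | CI width ratio (square root) |
|---|---|---|
| 0.3 | 2/1.3 = 1.54 | 1.24 |
| 0.5 | 2/1.5 = 1.33 | 1.15 |
| 0.7 | 2/1.7 = 1.18 | 1.08 |
| 0.8 | 2/1.8 = 1.11 | 1.05 |

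**Step 5: precision, unequal SDs.** With k = baseline SD / follow-up SD, the ratio becomes

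(k² + 1 − 2ρk)/(1 − ρ²)

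Entry only above 7% cuts off the lower part of the baseline HbA1c distribution, so k may be below 1. At an assumed k = 0.8:

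- ρ = 0.6: (0.64 + 1 − 0.96)/0.64 = 0.68/0.64 = 1.06
- ρ = 0.5: (0.64 + 1 − 0.80)/0.75 = 0.84/0.75 = 1.12

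Under equal SDs the same correlations give 2/1.6 = 1.25 and 1.33. If k were above 1, the loss would be larger than under equal SDs. The entry threshold does not act directly on dietary adherence, the other primary outcome.

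**The case against.** The best defence is that the article condenses a fuller plan and does not say how baseline enters. A baseline-by-time term would change the test, as step 2 shows, and would recover much of the ANCOVA gain. That stands as a limit: the no-effect result is exact only for a main effect with complete data. It does not remove the point, because the article does fix baseline as a response level and does state an adjustment, and the plain reading of the two together achieves nothing for the interaction.

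Several stronger readings are tempting, and the documents do not support them.

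- *The test gives false positives, or ignores baseline.* It does neither. Type I error holds, and a change-from-baseline comparison takes account of baseline, only less efficiently.
- *The 6-month question cannot be answered.* The Bonferroni comparisons are unlisted and could include the 6-month contrast, and the 12-month hypothesis gives a reason to model both visits. The fault is that the contrast is not named.
- *The trial loses a definite amount of power.* The documents give no SD, correlation or effect size, and a pilot of this size was not set by power. With a high correlation and an effect sustained to 12 months, the overall test can do as well as a 6-month ANCOVA: both had 89% power at an assumed ρ of 0.8 and a sustained effect of 0.5 SD.
- *The t-tests are a rival primary analysis, or the normality tests switch everything to rank methods.* The t-tests follow the descriptive summaries, and the ANOVA is introduced separately for change over time. The wording "with non-parametric methods applied as appropriate" names no rank method and does not say that the ANOVA would be replaced.

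**Conclusion.** The point holds, at moderate severity. As written, the group-by-time test is an unadjusted comparison of change from baseline, and the stated baseline adjustment does not reach it. This rests on baseline entering as a main effect and on complete data.

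The consequence is a less precise estimate of the treatment effect, not an invalid test. With equal SDs, the 6-month contrast has 11% to 54% more variance than ANCOVA over assumed correlations of 0.8 down to 0.3, which makes its interval about 5% to 24% wider. For HbA1c the excess may be only about 6% to 12% if the entry threshold reduces the baseline SD to 0.8 of the follow-up SD, at correlations of 0.6 to 0.5. All of these correlations and SD ratios are assumptions, because the article gives none.

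Separately, the contrast that answers the 6-month hypothesis is left unnamed among unlisted post hoc comparisons.

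**What to change.** Take baseline out of the responses and keep it as a covariate. Fit a longitudinal model to the follow-up visits with arm, visit, arm × visit, baseline and baseline × visit. A constrained longitudinal model, which keeps baseline as a response but gives both arms a common baseline mean, is an acceptable alternative. One of the two should be stated.

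For each primary outcome, name the adjusted arm difference at 6 months, with its 95% CI, as the primary contrast, and the adjusted difference at 12 months as the maintenance contrast. List any further comparisons to which the Bonferroni adjustment applies.

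The cost is a few sentences of analysis text. No patients, visits or measurements are added.
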